## **2.4. Study Aims**

**Primary Aim:** To assess if the RFPM can accurately estimate simulated food intake compared to the gold standard— directly weighed foods.

**Secondary Aim:** To evaluate the inter- and intra-individual variability in infant formula preparation.

**Exploratory Aim:** To investigate the variability in infant formula preparation between caregivers and non-caregivers of infants. A caregiver will be defined as an individual who is a parent, grandparent, sibling, aunt or uncle, or nanny or babysitter who has provided care to an infant within the last 12 months.

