### **7.4. Directly Weighed Food Method**

The directly weighed food method is a useful method for estimating food intake and simulated waste in research and clinical settings. The formula bottle with powdered formula, the prepared formula bottle, and the formula bottle after discarding waste will be directly weighed to the tenth of a gram using METTLER TOLEDO PB3001 scales in the IBL.

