## **9. DATA ANALYSIS PLAN**

### **9.1. Power Analysis**

We will test the primary aim to assess if the RFPM can accurately estimate simulated food intake compared to the gold standard— directly weighed foods. Power calculations were performed on the main outcome variable, which is the simulated food intake. Two measures of food provision will be obtained: powdered formula and prepared formula, the latter of which is created by adding water to the powdered formula. Food waste is defined as the liquid formula remaining in a bottle after simulating feeding (random discard of 10-90% of prepared bottle). Food intake is food provision minus food waste. A secondary aim is to evaluate the inter- and intra- individual variability in infant formula preparation so this study is also appropriately powered to detect differences in the grams of powdered dry formula in the bottle.

A power analysis was conducted for the Bland and Altman procedure that will be used to determine if the RFPM significantly over or underestimates food provision, waste, or intake and if the error associated with the RFPM varies over the amount of food provision, waste, and intake. Determining if error variance differs over levels of intake is critical to examining validity and accuracy; hence, the sample size was established based on the regression analysis used to do so since it required the largest number of participants.

A power analysis was conducted for the Bland-Altman regression analysis. The power analysis indicated that an  $R^2$  of .14 can be detected with 53 participants (power = .80) and this is considered acceptable based on studies that used Bland-Altman analysis on biological parameters. This research indicates that poor measures frequently have  $R^2 \geq 0.16$ ; therefore, sample size of 53 would yield satisfactory statistical power in the analyses for the primary aim. The primary aim was used for power calculations since sample size was based on the least powered endpoint (i.e. aim 1).

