Paired dependent t-tests will determine if the RFPM has significant error; i.e., if RFPM estimates differ significantly from weighed food. Variance estimates for the power analyses were obtained from our laboratory [10] and assumptions included alpha equal to 0.05, two-tailed tests, and anticipated sample size with 5% attrition (56 subjects will begin the study anticipating we will have a final sample size of 53 subjects.) Again, power of .80 was considered acceptable.

Power for intake (provision minus waste) of prepared formula was calculated with variance estimates for intake of beverages from our laboratory. As illustrated in Table 2, with 53 participants and the assumptions listed above, we have 80% power to detect a 4.95 g difference between RFPM estimated and directly weighed prepared formula intake.

| Table 2. Effect Size Calculations for Intake (Provision minus Waste) of Beverages |                                                     |        |       |             |
|------------------------------------------------------------------------------------------|-----------------------------------------------------|--------|-------|-------------|
| n per group                                                                              | Minimum detectable difference in formula weight (g) | SD (g) | Power | Effect Size |
| 30                                                                                       | 6.80                                                | 9.71   | 0.80  | 0.70        |
| 40                                                                                       | 5.83                                                | 9.71   | 0.80  | 0.60        |
| 45                                                                                       | 5.44                                                | 9.71   | 0.80  | 0.56        |
| 50                                                                                       | 5.15                                                | 9.71   | 0.80  | 0.53        |
| 53                                                                                       | 4.95                                                | 9.71   | 0.80  | 0.51        |
| 55                                                                                       | 4.86                                                | 9.71   | 0.80  | 0.50        |

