| 60                                                                                       | 4.66                                                | 9.71   | 0.80  | 0.48        |

With 53 subjects, we can detect a difference of 2.57 g (effect size or ES = 0.55, Table 3) between the RFPM's estimate and the weighed value for provision of powdered infant formula. This power analysis relied on variance estimates for condiments from our laboratory [10] which are similar to infant formula. This effect size of 2.57 grams reflects a very small amount of formula, indicating that the study is sufficiently powered. We recognize that predicting that no significant differences will be detected is problematic, though the proposed sample size and data analytic plan represents a viable alternative to equivalence tests that require very large sample sizes.

| Table 3. Effect Size Calculations for Food Provision (Dry Weight) |                                                     |        |       |             |
|--------------------------------------------------------------------------|-----------------------------------------------------|--------|-------|-------------|
| n per group                                                              | Minimum detectable difference in formula weight (g) | SD (g) | Power | Effect Size |
| 30                                                                       | 3.51                                                | 4.68   | 0.80  | 0.75        |
| 40                                                                       | 3.00                                                | 4.68   | 0.80  | 0.64        |
| 45                                                                       | 2.81                                                | 4.68   | 0.80  | 0.60        |
| 50                                                                       | 2.62                                                | 4.68   | 0.80  | 0.56        |
| 53                                                                       | 2.57                                                | 4.68   | 0.80  | 0.55        |
| 55                                                                       | 2.53                                                | 4.68   | 0.80  | 0.54        |
| 60                                                                       | 2.39                                                | 4.68   | 0.80  | 0.51        |

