## 9.2. Data Analysis

Paired dependent t-tests will determine if the RFPM has significant error; i.e., if RFPM estimates differ significantly from weighed food, and the Bland and Altman regression procedure will be conducted to determine if error variance differs over the amount of food provision, waste, and intake. Provision, waste, and intake will be compared using paired t-tests. Also, provision, waste, and intake will be compared using the Bland-Altman method. Statistical significance will be set at an alpha of 0.05.

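### The Bland-Altman amount-trend regression does not name its predictor; if the usual average of the two methods is used against a near error-free scale, the slope test is biased upward

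*Protocol*

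**What the plan says.** The primary aim in section 2.4 is to see whether the RFPM can "accurately estimate simulated food intake compared to the gold standard", which is directly weighed food. Under section 7.4 the bottles "will be directly weighed to the tenth of a gram using METTLER TOLEDO PB3001 scales".

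Section 9.1 bases the sample size on a Bland-Altman regression that asks whether RFPM error changes with the amount of provision, waste and intake. It calls that question critical to validity. An R² of .14 "can be detected with 53 participants (power = .80"), and an R² of 0.16 or more is taken as the mark of a poor measure. Section 9.2 repeats the regression, sets alpha at 0.05, and adds that "provision, waste, and intake will be compared using the Bland-Altman method".

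Both sections describe the predictor only as the amount. Neither says whether that is the average of the two methods or the weighed value.

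**The concern.** Plotting and regressing the difference on the average suits two methods with comparable error. It does not suit a comparison with a reference that has almost none. Write W for the weighed amount and RFPM = W + e. The difference is then e and the average is W + e/2. The same error sits on both axes, so the slope is positive by construction even when e is unrelated to W.

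Two wrong conclusions can follow. A photograph method whose error does not depend on amount may be reported as having amount-dependent error. A method that truly under-reads larger amounts may appear free of trend, because the artefact is always positive and cancels a negative slope. For a validation study the second is at least as serious. Both would arise in the analysis that fixed the sample size.

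**Working it through.** **Inputs from the protocol**
- Alpha and sidedness (9.1): "assumptions included alpha equal to 0.05, two-tailed tests".
- Participants (9.1): "56 subjects will begin the study anticipating we will have a final sample size of 53 subjects".
- Powder SD (9.1, Table 3, row for 53): "4.68 | 0.80 | 0.55", that is 4.68 g. On its source: "This power analysis relied on variance estimates for condiments from our laboratory". The protocol does not say whether it is an SD of differences.
- Intake SD (9.1, Table 2): 9.71 g.
- Label powder amounts (6.2): 8.8, 17.6, 26.4 and 35.2 g. With the four sizes equally represented, SD = 8.8 × √1.25 = 9.84 g.
- Bottles (6.2, 6.3): 8 + 4 = 12 per participant; 53 × 12 = 636.
- Scale resolution (7.4): 0.1 g, a rounding SD of 0.1/√12 ≈ 0.03 g, negligible beside 4.68 g.

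**The plan's own figures.** For one slope with R² = .14 and n = 53, the noncentral F test (f² = R²/(1 − R²), λ = n f²) gives power 0.822; the Fisher z formula gives 0.794. The stated .80 is reproduced. Attrition also agrees: 53/0.95 = 55.8, rounded up to 56.

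**Artefact with no true trend and the average as predictor**

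Slope = ½σₑ² / (σ_W² + ¼σₑ²); R² = ¼σₑ² / (σ_W² + ¼σₑ²)

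Powder, σₑ = 4.68, σ_W = 9.84: ¼σₑ² = 5.48 and σ_W² = 96.80. Slope = 10.95/102.28 = 0.107; R² = 5.48/102.28 = 0.054; r = 0.231.

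If 4.68 g is instead each method's own SD, the SD of differences is 4.68 × √(2(1 − r)): 2.96 g at r = 0.8 (R² = 0.022) and 2.09 g at r = 0.9 (R² = 0.011), keeping the amount SD at 9.84 g.

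Intake, σₑ = 9.71, so ¼σₑ² = 23.57. The amount SD is not in the protocol. Assuming 29.57 g of water per fluid ounce and a uniform discard over the stated 10-90%, it is about 50 g for water alone (R² = 23.57/2523.57 = 0.009) and about 57 g with powder mass added (R² = 0.007).

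**Rejection rate of the two-sided 5% slope test, no true trend, average as predictor**

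| Case | One bottle each, n = 53 | All 636 bottles pooled |
|---|---|---|
| Powder, SD of differences 4.68 g | 39.7% (simulated 38.4%) | about 100% |
| Powder, own SD 4.68 g, r = 0.8 | 19% | 97% |
| Powder, own SD 4.68 g, r = 0.9 | 12% | 76% |
| Intake, amount SD 50 g | 11% | 69% |
| Intake, amount SD 57 g | 9% | 57% |

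With the weighed amount as predictor, simulated rates stay at about 5%. In the first powder case, giving the four sizes near-equal numbers instead of drawing them at random moves the average-based rate from 38.4% to 36.6%.

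**Participant means.** Everyone prepares the same sizes, so means differ only through between-person preparation spread, which the protocol does not give. For powder with SD of differences 4.68 g and assumed preparation CVs of 5%, 10% and 20%, the rates are 98%, about 58% and 18% with uncorrelated errors. With an assumed within-person error correlation of 0.2 they are 100%, 95% and 49%.

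**Masking.** Suppose the RFPM under-reads powder by 12% of the amount: difference = −0.12W + e, average = 0.94W + e/2. Their covariance is −0.12 × 0.94 × 96.80 + ½ × 21.90 = −10.92 + 10.95 ≈ 0. The artefact cancels the true trend. At n = 53 with SD of differences 4.68 g, the trend is detected in about 4% of simulated studies using the average and about 43% using the weighed amount.

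**Benchmark.** In null powder studies (one bottle each, SD of differences 4.68 g) the sample R² reaches 0.16 in about 9% using the average, against 0.2-0.3% using the weighed amount.

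**The case against.** A reader might infer that the protocol prescribes the average and that a 39% false-positive rate follows from its own figures. The text supports neither. It speaks only of the amount, which fits the weighed value equally well, and an analysis plan not seen here may settle the predictor. The 39% needs three assumptions that the protocol does not make: that 4.68 g is the SD of differences, that each participant contributes one bottle, and that the four sizes are equally represented. The first is doubtful. The SD comes from condiments, and Table 3's 2.57 g at 53 per group reproduces only as a two-sample test; a paired test with an SD of differences of 4.68 g would detect 1.84 g. Nor does the design match one bottle each.

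A reader might also infer that the 0.16 benchmark is largely made of artefact. It is not: the expected artefact R² is 0.054 for powder and under 0.01 for intake. Nor is near-certain false rejection on participant means established, since it depends on an unstated spread. And simulated intake, the main outcome, is only mildly affected with one bottle each.

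All of that stands and limits the size of the point. It does not remove it. The protocol commits to a named procedure whose usual predictor is the average and applies it against what it calls a gold standard. A reader following the name would use the average, and every reading computed above then exceeds 5%.

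**Conclusion.** The point holds conditionally. Sections 9.1 and 9.2 leave the predictor of a sample-size-setting regression unnamed, and the named method's usual choice is unsuitable against a near error-free reference. If the average is used, the 5% slope test at n = 53 with one bottle each rejects in about 38-40% of null powder studies (4.68 g as SD of differences), or about 12-19% (4.68 g as each method's own SD, correlation 0.9-0.8). For intake it is about 9-11%. Pooling 636 bottles gives about 76-100% for powder and 57-69% for intake; participant means give about 18-100% for powder.

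These figures assume error of constant SD unrelated to amount, an error-free scale, an amount SD of 9.84 g for powder and an assumed 50-57 g for intake. The inflation concerns the alpha 0.05 test much more than the 0.16 benchmark. The stated sample size of 53 is not itself in question here.

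**What to change.** Add one phrase to section 9.2: the regression of RFPM error on amount uses the directly weighed amount as predictor, for provision, waste and intake alike. Keep the plot of difference against average as a descriptive figure, without a slope test attached. No extra data or participants are needed. The only cost is a small departure from the usual plotting convention, which one sentence on the gold-standard reference would justify.

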## 10. SUBJECT PAYMENT

Subjects enrolled in this study will receive \$20. The full payment will be paid after completion of the 2 study visits. If participants drop out of the study or are withdrawn prior to completion of Visit 2, the participants will receive \$10 for the completion of Visit 1. The compensation is in line with all the other studies conducted at the PBRC.

